### Sample size and sampling

Based on current rates of the CBCT programme, which were used to come up with targets for the SF model, data will be analysed after 12 months of programme implementation. Each arm will have 19 counsellors recruiting at least 100 clients per counsellor per month for 12 months excluding weekends and holidays. Requiring counsellors to test 100 clients per per month is a conservative assumption that considers SFs as new players in conducting CBCT to emphasize accuracy and quality in CBCT work. Based on this assumption and calculation, a total of 91,200 participants are expected to be recruited in 24 months and half of these (45,600) will be recruited by SFs while the other half by FPD. A 12-month follow up and a final 24 months evaluation to assess programme effectiveness will be conducted. No randomisation of counsellors or clients will be done. All sub districts were selected based on current rates of HIV infection, which is highest in the townships where predominantly black Africans reside.

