## Methods

### Design

The study is a two arm non-randomised community implementation trial with a once off round of post-test follow-up per HIV positive participant to assess linkage to care. Clients will be tested by one of the HIV testing strategies – either by an existing FPD counsellor or a SF HIV counsellor under the sub-contracted model. Each study arm has 19 counsellors conducting CBCT. The overall study design is illustrated on Table 2.

**Table 2 Tab2:** Process flow for the FPD and Social Franchise HTS

Item	Activity	FPD	Social franchise
1. Counsellor Recruitment and contracting	Contract	1. Employed by FPD 2. Normal employment contract 3. Normal payroll contract 4. Work for 8 h a day	1. Unemployed, self-employed or employed elsewhere, not employed by FPD 2. Contracted by franchisee-franchisor contract 3. No restriction on hours, days worked 4. Test >/= 100 people per month 5. Test>/5 HIV + tests per month 6. Link >/= 4 HIV + clients per month
	Remuneration	1. Fixed monthly salary	1. Paid $3.20 per HIV test 2. Paid $8 per HIV + client linked
	Training	Training focussed on: 1. Pre-test, test, post-test, documentation, referral and linkage to care	Training focussed on: 1. Pre-test, test, post-test, documentation, referral and linkage to care 2. business development & management
2. Mobilisation	Community level mobilisation	Community events; flyers; campaigns (e.g. couples counselling); conducting systematic door-to-door mobilization campaigns distributing flyers, and condoms	Community events; flyers; campaigns (e.g. couples counselling); conducting systematic door-to-door mobilization campaigns distributing flyers, and condoms
	Individual level mobilisation	Informing households on the benefits and availability of testing for HIV; scheduling household level testing appointments and/or actively recruiting clients for same day HTS	Informing households on the benefits and availability of testing for HIV; scheduling household level testing appointments and/or actively recruiting clients for same day HTS

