SFs will be remunerated per specific measurable work activities done in order to track progress and measure costing of the project, while also delivering agreed outputs and maintaining the brand. As such, R40^1^ will be paid per HIV test conducted. This amount remunerates a basic package of HTS services to each client tested that includes consenting a client, conducting an HIV test, distributing condoms, providing client tailor made HIV prevention messages and relevant referrals,^2^ screening for TB and STI and subsequently making necessary referrals, documenting the client. A second, and much bigger remuneration, of R100 will be paid for every HIV positive client linked to HIV care and treatment programmes in the health system. This larger amount is aimed at motivating linkage to care which proved challenging for most counsellors implementing CBCT programmes in the country [33, 34]. SFs will be contracted to test a minimum of 100 clients per month. This minimum requirement was determined by calculating the average time required to conduct HIV testing of an average of 5 people per day while allocating time to conduct other duties including mobilisation, documentation and business management aspects. In order to motivate the SFs to study communities to identify and target HIV hotspots [35, 36], it is a contractual requirement to find at least 5 HIV positive individuals in the 100 people tested. This translates to a minimum 5% HIV positivity target in Tshwane district. The target for linkage to care was at least 4 (80%) of the 5 HIV positive clients being linked to care. Consideration was made of the challenges of linkage to care based on FPD’s experience of running the CBCT programme. The project will review the targets upwards once SFs demonstrated delivery of adequate and quality work in order to align to the UN 90–90-90 target for South Africa to link 90% of the HIV positive people identified [30, 37]. Regular (weekly, bi-monthly, monthly, and quarterly) reports, field visits and observations will be made by FPD to monitor program performance and address any challenges. FPD will audit the SFs’ work and provide regular feedback to SFs to assess their progress. The same linkage to care process as in the FPD HTS will be followed by counsellors.

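### The sample size paragraph gives two recruitment periods, 12 and 24 months, that differ by a factor of 2 in expected numbers, and does not say which of its two analysis times carries the effectiveness conclusion

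*Protocol article*

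**What the plan says.** All the conflicting statements stand in one paragraph of the protocol article, under Sample size and sampling.

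- Analysis time, first statement: "data will be analysed after 12 months of programme implementation".
- Recruitment inputs: "Each arm will have 19 counsellors recruiting at least 100 clients per counsellor per month for 12 months excluding weekends and holidays".
- Stated total: "Based on this assumption and calculation, a total of 91,200 participants are expected to be recruited in 24 months".
- Split by arm: "half of these (45,600) will be recruited by SFs while the other half by FPD".
- Analysis time, second statement: "A 12-month follow up and a final 24 months evaluation to assess programme effectiveness will be conducted".

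The Design section confirms the other inputs: "The study is a two arm non-randomised community implementation trial", and "Each study arm has 19 counsellors conducting CBCT".

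The Follow up section expects follow-up at 6 weeks after testing and lets tracing for linkage run to six months. The Intervention arm section sets a contractual minimum of 5 positives per 100 tests, with 4 of those 5 linked to care. Neither the Abstract nor the Data analysis section names a recruitment period or an analysis time, so nothing elsewhere in the article settles the matter.

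**The concern.** The total is presented as following from the inputs just above it, but those inputs specify 12 months and the total needs 24. Both cannot be the recruitment period. No sentence says that recruitment continues for a second 12 months.

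The analysis time has the same problem. The paragraph opens with an analysis after 12 months and closes with a final evaluation at 24, and it gives neither a stated role.

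Two things are at stake. First, a reader cannot tell how large the trial is meant to be, so a report of about 45,600 tests in total could be read as a completed trial or as half of one. Second, linkage to care is a primary outcome that accrues over up to six months after the test. Its value at a given cut depends on how many positives have had that time, and hence on both the recruitment period and the cut. Leaving both open also leaves room to choose the main result after the 12-month data have been seen.

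**Working it through.** **Inputs.** Arms: 2 (Design). Counsellors per arm: 19 (Design; Sample size and sampling). Clients per counsellor per month: 100, the stated minimum (Sample size and sampling). Months: 12 or 24, both in Sample size and sampling. Positives per counsellor per month: 5, the social franchise contract minimum (Intervention arm), applied here to both arms for illustration. Tracing window: six months (Follow up).

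**The plan's own figure.** Total = arms × counsellors × clients per month × months.

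- With 24 months: 19 × 100 × 24 = 45,600 per arm; 2 × 45,600 = 91,200. This reproduces both printed numbers exactly.
- With the stated 12 months: 19 × 100 × 12 = 22,800 per arm; 2 × 22,800 = 45,600. This is half the printed total.

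**Expected positives per arm** = 19 × 5 × months.

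- 12 months: 19 × 5 × 12 = 1,140.
- 24 months: 19 × 5 × 24 = 2,280.

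**Positives with a closed six-month window.** This assumes even accrual and data locked exactly at the cut; the article states neither.

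| Recruitment | Cut | Positives per arm | Window closed | Window still open |
|---|---|---|---|---|
| 12 or 24 months | month 12 | 1,140 | 19 × 5 × 6 = 570 | 570 (one half) |
| 24 months | month 24 | 2,280 | 19 × 5 × 18 = 1,710 | 570 (one quarter) |
| 12 months | month 24 | 1,140 | 1,140 | 0 |

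The share of positives with an open window thus runs from none to one half, depending on which of the article's statements is followed.

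**Effect on precision.** For the between-arm difference in linkage at the 80% target, analysed by client, the 95% half-width is 1.96 × √(2 × 0.8 × 0.2 / n). That is 3.3 percentage points at n = 1,140 and 2.3 at n = 2,280. Outcomes may also cluster by counsellor. The article gives no intracluster correlation (ICC), so a range is assumed. The variance is multiplied by 1 + (m − 1) × ICC, where m = 1,140/19 = 60 or 2,280/19 = 120 positives per counsellor, and 1.96 is replaced by t with 36 degrees of freedom (2.028).

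| Assumed ICC | 12 months | 24 months |
|---|---|---|
| 0.01 | ±4.3 points | ±3.6 points |
| 0.05 | ±6.8 points | ±6.3 points |
| 0.10 | ±8.9 points | ±8.6 points |

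Once clustering is allowed for, doubling the period adds little precision for linkage. The main harm is the unsettled period and cut.

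**The case against.** The strongest reply is that the paragraph can be read coherently. The sentence with the total names its own period, and the total is exact for it. The assumption mentioned just before it is the rate of 100 clients a month, which does not depend on 12 or 24 months. The word final, attached to effectiveness at 24 months, points to that evaluation as the concluding one and to month 12 as an earlier look. The formal role of an interim look is often left to the full protocol or SAP, which are not shown.

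Much of this stands, and it limits the point. A reader might infer a multiplication error; there is none. A reader might infer that the printed 45,600 is ambiguous between one arm and the whole trial; the text labels it as per arm, and the coincidence with the total appears only when 12 months is put into the formula.

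A reader might also infer that the two cuts would describe different contracts, because "The project will review the targets upwards once SFs demonstrated delivery of adequate and quality work". The article gives no date for that review and no change in fees, so this is speculation. Nor does an open tracing window mean an unknown outcome: follow-up is expected at 6 weeks, so many clients will already have a linkage status.

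What the reply does not remove is the sentence that sets recruitment at 12 months, or the opening statement that data will be analysed after 12 months. The coherent reading has to override both, and the article never says that it does. This is a printed contradiction, so condensing a longer protocol into an article does not excuse it.

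**Conclusion.** The point holds as an internal contradiction in the recruitment period, together with two analysis times whose roles are not stated. The stated inputs give 22,800 per arm and 45,600 in total; the stated totals of 45,600 per arm and 91,200 hold only for 24 months of recruitment. The factor of 2 follows from the article's own numbers and needs no assumption.

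The 1,140 v 2,280 positives per arm rest on the 5% contract minimum, which binds only the social franchise arm. The one half of positives with an incomplete tracing window at month 12 rests on even accrual and a data lock at exactly 12 months. The article shows no power calculation that uses the totals, and the 24-month evaluation is the more likely intended conclusion. The paragraph should be corrected, but the contradiction does not by itself invalidate the design.

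**What to change.** Reword the paragraph under Sample size and sampling to do three things.

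1. State one recruitment period with its matching total: either 24 months with 45,600 per arm and 91,200 in total, or 12 months with 22,800 per arm and 45,600 in total. Give the expected positives per arm beside it (2,280 or 1,140 at the contract minimum).
2. Name one primary data cut. If recruitment is 24 months, make the 24-month evaluation primary and the 12-month look descriptive. If it is 12 months, say which evaluation is primary; all six-month windows would have closed by month 12 + 6 = 18.
3. At any cut, restrict the linkage analysis to positives whose six-month window has closed, and report how many are still within it.

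The cost is one reworded paragraph, with no added recruitment. If 12 months is what was meant, the stated total halves. Restricting linkage at a 24-month cut with 24 months of recruitment would set aside about 570 of 2,280 positives per arm, under even accrual, until their window closes.

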### Control arm - FPD HTS

In order to identify people infected with HIV (PLHIV) and bring them into HIV care, FPD designed and implemented a CBCT programme in 2013 that ran through 2018 [29]. The programme aimed to make significant inroads towards the UNAIDS’s 90–90-90 goal [30] through the alignment with the South African Government’s (SAGs) National Strategic Plan on HIV, STIs and TB (NSP 2012–2016) [31] and the PEPFAR/SA HIV Prevention Strategy [32]. To implement the CBCT strategy, FPD formally advertised and employed counsellors to conduct HTS. The counsellors attended a 10-day training programme covering HTS and linkage to HIV care including documentation, approaching communities, consenting as shown on Table 2. FPD managed counsellors’ daily HTS activities and remunerated them monthly without necessarily pegging the salary to HTS outputs. The client recruitment strategy for testing is described as home-based in which counsellors moved door-to-door recruiting clients in the community. FPD teams, who include a driver/counsellor and at least four other counsellors per team, drive from the office to the communities in the selected study/project sites daily to conduct HIV testing and travel back to the office. Counsellors will test and refer clients for linkage to care. Linkage to care will be confirmed by checking clinic registers and Tier.net, an electronic patient management system used for capturing patient-level data on HTS, pre-ART and ART services. Counsellors will follow up clients for up to six months to ensure that they are linked to care.

### Intervention arm - SF HTS or SFs

In 2016, FPD CBCT introduced a separate Social franchise testing model [27] into the existing CBCT approaches (See Table 2). The programme aims at assessing effectiveness of a community-based HTS study implemented through social franchisees in Tshwane district in Gauteng province, South Africa. The model aims at providing implementation evidence by assessing success or failure of the model to inform roll out through a public-private partnership between government and non-governmental organisations. As part of the recruitment process, FPD advertised and encouraged individuals and small-scale business people, either employed or unemployed, to apply for the SF opportunity. Applicants will be interviewed by an FPD recruitment and selection panel. Successful SFs will be provided with a 10-day training on HTS, documentation, referral for ART and business management. The training on small business management is aimed at ensuring SFs obtain skills in management of mall-scale business including CBCT resources, ordering and disbursing CBCT materials and ledger balancing. Each SF (*n* = 19) will sign a contract with FPD to deliver a standards-based product of CBCT (HIV testing and linkage to care package) to decide where to conduct HIV testing daily in the designated communities, decide demographics of people to target daily, mobilise communities, families and individuals regularly, recruit clients, test them, and to link HIV positive clients to referral health facilities within the communities per agreement with clients. SFs will deliver a common brand that FPD implements and systematizes. The role of the franchisor, FPD, will be to prescribe HTS standards, recruit, train and accredit SFs, including deregistering SFs that fail to meet prescribed CBCT brand/standards. FPD will also maintain quality assurance of the SFs through making announced and unannounced visits to the SF offices and areas of work. In addition, FPD will support the SFs by establishing linkages between SFs and the referral health facilities where the SFs will refer clients for HIV prevention, care and treatment. Furthermore, FPD will facilitate access to HTS commodities and waste disposal services, verification of linkage to HIV care and treatment, access to information, education and provide communication materials for HIV prevention and marketing as well as paying SFs in accordance with numbers tested and linked to care and treatment.

SFs will be remunerated per specific measurable work activities done in order to track progress and measure costing of the project, while also delivering agreed outputs and maintaining the brand. As such, R40^1^ will be paid per HIV test conducted. This amount remunerates a basic package of HTS services to each client tested that includes consenting a client, conducting an HIV test, distributing condoms, providing client tailor made HIV prevention messages and relevant referrals,^2^ screening for TB and STI and subsequently making necessary referrals, documenting the client. A second, and much bigger remuneration, of R100 will be paid for every HIV positive client linked to HIV care and treatment programmes in the health system. This larger amount is aimed at motivating linkage to care which proved challenging for most counsellors implementing CBCT programmes in the country [33, 34]. SFs will be contracted to test a minimum of 100 clients per month. This minimum requirement was determined by calculating the average time required to conduct HIV testing of an average of 5 people per day while allocating time to conduct other duties including mobilisation, documentation and business management aspects. In order to motivate the SFs to study communities to identify and target HIV hotspots [35, 36], it is a contractual requirement to find at least 5 HIV positive individuals in the 100 people tested. This translates to a minimum 5% HIV positivity target in Tshwane district. The target for linkage to care was at least 4 (80%) of the 5 HIV positive clients being linked to care. Consideration was made of the challenges of linkage to care based on FPD’s experience of running the CBCT programme. The project will review the targets upwards once SFs demonstrated delivery of adequate and quality work in order to align to the UN 90–90-90 target for South Africa to link 90% of the HIV positive people identified [30, 37]. Regular (weekly, bi-monthly, monthly, and quarterly) reports, field visits and observations will be made by FPD to monitor program performance and address any challenges. FPD will audit the SFs’ work and provide regular feedback to SFs to assess their progress. The same linkage to care process as in the FPD HTS will be followed by counsellors.

### Outcomes

The study has four primary outcomes for programme success: 1) *HIV testing uptake rate,* is defined as all clients who received a basic package of HTS, including HIV testing, divided by the total number of clients offered HIV testing multiplied by 100, 2) *HIV positivity* is defined as the number of clients testing HIV positive divided by the total number of clients tested for HIV multiplied by 100, 3) *Linkage to HIV care and treatment rate* is a proportion of all clients tested positive during the current reporting period and successfully linked to care, divided by the number of all HIV positive clients referred for linkage during the current reporting period multiplied by 100. 4) *Average Counsellors’ remuneration cost* per person tested, per HIV positive test and per person linked to care will be calculated to determine the average cost of employing counsellors in each study group per outcome described above. Secondary outcomes include 5) *App use rate,* is the total number of participants whose data were primarily captured on the app divided by the total number of clients tested multiplied by 100, 6) *First time HIV testers rate* is the proportion of persons identified as testing for HIV for the first time divided by the total number of people tested in a given period multiplied by 100, 8) *Couples HIV testing rate* is defined as the proportion of two people, identifying themselves as partners, testing and receiving results together divided by the total number of clients testing multiplied by 100.

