### Follow up

The purpose of participant follow-up in each arm is to collect linkage to care information from clients who tested HIV positive which include whether one is linked to care or not, date linked to care, result of linkage to care, services received (including initiation on antiretroviral treatment) and challenges to linkage to care and treatment, if any. Counsellors will extract and maintain a log of clients’ date of expected follow up – 6 weeks post-testing, clinic name, date of test and identification details including name, gender, age and national registration identity number. Counsellors will visit all referral clinics in the study community and collect these details which are entered into HIV testing registers. The information will be entered onto referral forms issued to the HIV positive clients during post-counselling and entered into the database. Those not yet linked to care will be called telephonically and or visited to encourage them to link with health facilities for treatment. A maximum of six attempts will be made to encourage participants to link with care before they are regarded as lost to follow up. The follow up process will be done within a period of six months post testing.

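### The primary linkage rate divides by clients referred rather than by all who tested positive, and sets no linkage window per client although follow-up runs to six months

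*Protocol article*

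**What the plan says.** The Outcomes section lists the linkage rate as the third of four primary outcomes. The numerator "is a proportion of all clients tested positive during the current reporting period and successfully linked to care"; this is "divided by the number of all HIV positive clients referred for linkage during the current reporting period multiplied by 100". Neither the reporting period nor a time limit from test to linkage is defined there.

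Other sections bear on the same quantity:

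- **Follow-up time.** The Follow up section has counsellors log a "date of expected follow up – 6 weeks post-testing" and then states: "The follow up process will be done within a period of six months post testing". The control-arm section agrees: "Counsellors will follow up clients for up to six months to ensure that they are linked to care". The franchise-arm section says the same linkage process applies there.
- **Population followed up.** The Follow up section collects linkage information on clients who tested positive, not only on those referred.
- **Targets.** The intervention-arm section states: "The target for linkage to care was at least 4 (80%) of the 5 HIV positive clients being linked to care". It foresees raising this to 90% of the positive people identified. Both targets count all positives.
- **Analysis times.** Under Sample size and sampling, "data will be analysed after 12 months of programme implementation", and a final evaluation follows at 24 months.
- **Referral.** Table 2 lists referral for treatment and care in the post-test package of both arms, and the Follow up section has referral forms issued to positive clients at post-test counselling. The section on the app gives positive clients one set of extra variables and referred clients a further set, so the two are recorded as separate steps.

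**The concern.** A linkage rate should say who is at risk of being counted, and by when. This one leaves both unsettled.

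**Denominator.** The numerator takes everyone who tested positive and linked; the denominator takes only those referred. These are different populations. If some positives are not referred, the rate exceeds linkage among all positives, and it can pass 100% if enough unreferred clients link. It also cannot be set against the protocol's own 80% and 90% targets.

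**Time.** With no window per client, the rate depends on when it is read. Clients tested shortly before the data cut are in the denominator before their follow-up is complete, which pulls the rate down.

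The two faults act in opposite directions, so the net error is unknown. The count of linked clients also enters the fourth primary outcome, through remuneration cost per person linked, so an early cut would affect that figure too.

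**Working it through.** **1. The plan's own figures.** Target: 4/5 = 80%, with all positives as the denominator. At the franchise contract minimum, 19 counsellors × 5 positives × 12 months = 1,140 positives and 19 × 4 × 12 = 912 linked; 912/1,140 = 80%. Recruitment: 19 × 100 × 24 months × 2 arms = 91,200, as stated.

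**2. Denominator.** Let P be positives, R referred and L positives who linked. The outcome is L/R and the target is L/P. Since L/P = (L/R) × (R/P), a reported 80% means:

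| Share referred, R/P (assumed) | Linkage among all positives |
|---|---|
| 100% | 80% |
| 95% | 0.80 × 0.95 = 76% |
| 90% | 0.80 × 0.90 = 72% |
| 80% | 0.80 × 0.80 = 64% |

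The documents give no referral share, so this is a range and not an estimate. L is not limited to referred clients, so the ratio is unbounded at 100%: 80% linked with 70% referred gives 0.80/0.70 = 114%.

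**3. Incomplete follow-up at the planned analyses.** With even testing over L weeks and status read at the end, the share of positives with less than 26 weeks of follow-up is 26/L:

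- 12 months: 26/52 = 50%
- 24 months: 26/104 = 25%

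**4. Effect on the rate.** Assumptions: true linkage is 80% at 26 weeks in both arms, and time to linkage is exponential with a median of about 6 weeks, rescaled to reach 80% at 26 weeks.

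- λ = ln 2/6 = 0.1155 per week, and 1 − exp(−26λ) = 0.9504.
- The most recent 26 weeks of testing contribute (26 − 0.9504/0.1155)/0.9504 = 18.70 equivalent full weeks. Earlier weeks count in full.
- 12 months: 0.80 × (18.70 + 26)/52 = 68.8%.
- 24 months: 0.80 × (18.70 + 78)/104 = 74.4%.

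Range over other linkage patterns: 60% (linkage spread evenly over six months) to 76% (median 2 weeks) at 12 months, and 70% to 78% at 24 months.

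**5. Difference between arms.** Same model, one arm steady. In the other, testing rises linearly from zero to full pace and then stays level. True linkage is 80% in both.

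| Pace in the second arm | 12-month reading and gap | 24-month reading and gap |
|---|---|---|
| Same as first (as planned) | 68.8%, gap 0 | 74.4%, gap 0 |
| 3-month ramp | 67.2%, 1.6 pp | 74.0%, 0.4 pp |
| 6-month ramp | 65.0%, 3.7 pp | 73.6%, 0.8 pp |
| Linear over the whole period to the cut | 60.2%, 8.5 pp | 69.4%, 4.9 pp |

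**The case against.** **Truncation is not stated.** In the definition, the reporting period attaches to testing and to referral, not to linkage. It can be read as a cohort rate: positives tested in the period, linked at any time in their six months of follow-up. On that reading truncation disappears once every window has closed. This stands, so a reader should not infer that the rate is certainly truncated. But the definition does not say it is a six-month cohort rate, and an analysis made at 12 months would still meet open windows for half of the positives.

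**Monitoring reports are not the trial analysis.** The article lists "Regular (weekly, bi-monthly, monthly, and quarterly) reports", and a reader might infer that the outcome is read monthly or quarterly. No positive tested within a month reaches the 6-week date by its end, and 6/13 = 46% of those in a quarter do not. But those reports serve programme monitoring. The evaluations are at 12 and 24 months, so these figures do not apply to the comparison of arms.

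**A gap of about 9 pp between arms is not supported.** It needs one arm to build up linearly for the whole first year while the other is steady. The article describes no such ramp; it plans 19 counsellors per arm at no fewer than 100 clients a month each. At that pace the gap is 0.

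**Referral is meant to be universal.** Table 2 and the Follow up section intend every positive to be referred, so inflation is possible rather than shown. An unreferred client who links still counts in the numerator, so such clients do not simply vanish. This stands too. It also means that changing the denominator to all positives costs nothing if referral is complete.

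**Detail may sit in an unseen analysis plan.** Data-cut rules often do. The mismatch of populations, however, is in the outcome definition that the article itself prints.

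**Conclusion.** The definition of primary outcome 3 needs correction. Two facts rest on the text alone: the numerator and denominator cover different populations, with the denominator at odds with the targets and the follow-up population; and no linkage window is given per client although follow-up runs to six months.

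The sizes are conditional. The denominator changes a reported 80% to 72% of positives if 90% are referred, and changes nothing if all are. Reading status at the cut leaves 50% (12 months) or 25% (24 months) of positives with less than six months of follow-up under even testing, and 80% reads as about 69% or 74% under the exponential assumption.

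Bias between arms requires a difference in testing pace, linkage timing or referral recording. A 3- to 6-month ramp-up in one arm gives about 1.6 to 3.7 pp at 12 months and under 1 pp at 24 months. Different referral recording is conceivable, since franchisees are paid per client linked and control counsellors are salaried, but the documents do not show it.

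**What to change.** Redefine outcome 3 as the number of clients linked within six months of their own test date, divided by all clients with a confirmed positive test. Include only clients tested at least six months before the data cut, or estimate six-month linkage by Kaplan-Meier with censoring at the cut. Apply the same rule in both arms and at both the 12- and 24-month analyses. Report the share of positives referred, and linkage among those referred, as supplementary cascade steps. Use the same linked count in the cost per person linked.

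The cost is revised outcome wording. Test and linkage dates are already collected, so trial conduct does not change. The linkage analysis either waits up to six months after the last test or leaves out the most recently tested clients.
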